### Participants

The study will be conducted at the Affiliated Hospital of Zunyi Medical University in Zunyi, Guizhou Province. It is a 2,800-bed general hospital with over two million outpatient attendances per year. An average of 80–100 adolescent PCOS patients are seen at the gynecological clinic per month, providing the sample size required for this study.

### Patient recruitment

Adolescents with PCOS who attend the gynecology clinic of the Affiliated Hospital of Zunyi Medical University from January 2022 to August 2022 will be selected as the potential participants using a consecutive enrollment method. The final participants will be identified based on inclusion and exclusion criteria, and data are collected as both a training dataset and a validation dataset for the model construction. Data collected from September 2022 to December 2022 as an external validation cohort. Participants listed above will comprise the experimental group. Additionally, a control group will be recruited from the gynecology clinic among healthy, age-matched adolescent girls.

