**Methods and analysis:**

Model development and validation will be conducted using a retrospective study. The study will involve normal adolescent girls as the control group and adolescent PCOS patients as the experimental group. We will collect not only general factors such as individual susceptibility factors, biological factors, and psychosocial environmental factors of depression in adolescence, but will also examine the pathological factors, illness perception factors, diagnosis and treatment factors, and symptom-related factors of PCOS, as well as the outcome of depression. LASSO will be used to fit a multivariate warning model of depression risk. Data collected between January 2022 and August 2022 will be used to develop and validate the model internally, and data collected between September 2022 and December 2022 will be used for external validation. We will use the C-statistic to measure the model's discrimination, the calibration plot to measure the model's risk prediction ability for depression, and the nomogram to visualize the model.

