## Introduction

Polycystic Ovary Syndrome (PCOS) is a female endocrine metabolic disease of unknown etiology, with a prevalence of 5.6 to 11.04% in adolescence (1) and 10.26% in the Chinese adolescent population (2). Symptoms of PCOS include abnormal menstruation, infertility, hyperandrogenismia, and polycystic ovarian changes (3). It has been controversial and challenging to diagnose PCOS during adolescence due to the overlap between regular pubertal physiological changes (irregular menstrual cycles, acne, and polycystic ovarian morphology on pelvic ultrasound) and adult PCOS diagnostic criteria. Consensus statements on adult and pediatric health have acknowledged these challenges (4–6). To be more specific, challenges include the risk of under-diagnosis, delayed and/or poor diagnosis experiences (7), and over-diagnosis, as well as the additional risk of the use of inconsistent non-evidence-based approaches to PCOS diagnosis and management (8). PCOS generally begins after the first menarche in adolescence and lasts through the reproductive years and perimenopause. Besides affecting reproductive health, PCOS increases the risk of diseases such as type 2 diabetes, cardiovascular disease and endometrial cancer (9), as well as the development of psychiatric disorders. Adolescent girls with PCOS are 2.4 times more likely to suffer from depression than normal girls of the same age, about 50–60% (10, 11). A depressive disorder can result in great psychological and physical distress in adolescents, leading to suicide in over half of them, and it can affect the health and psychosocial functioning of adults as well (12). Studies have shown that PCOS can also lead to infertility in the long run (13). Nevertheless, recent studies suggest that PCOS on its own is not necessarily a cause of infertility (14). It is possible that infertility can be exacerbated by emotional and psychiatric problems in PCOS patients due to illness and fear of future infertility (14). Thus, it is recommended that psychological, emotional, and other non-medical measures be optimized in order to treat infertility, as well as increasing the attention given to depression in individuals with PCOS. PCOS, however, has no identified etiology and no specific treatment. Life management is recommended by international evidence-based guidelines as the ideal treatment for PCOS (15), but patients with the disorder have poor life management skills (16). The guideline declares that patients with PCOS can participate in better life management by improving their psychological status (4). There is no doubt that depression is a significant health issue that must be addressed in the management of adolescents with PCOS.

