The development of warning models often involves the incorporation of influencing factors. However, a variety of factors affect depression in adolescents, including: (i) biological factors, such as hormones and individual development during adolescence, which modifies neuroendocrine regulation and brain structure in diverse ways, contribute to adolescent depression. For instance, altering the activity of the hypothalamic-pituitary-adrenocortical (HPA) axis, affecting the release of neurotransmitters, altering the REM sleep latency, and so on, can all have an impact on the neurological structure and psychological state of the adolescent population, eventually leading to depression (19); (ii) individual susceptibility factors, such as genetic factors, with heredity influence approximately 40–50% of depressed people. Depressed people's first-degree relatives have a 10–13% chance of developing depression (20); (iii) psychosocial environmental factors, such as family environments, social development and social role changes, and negative behavior patterns, contribute to a sense of helplessness, which leads to negative attributions and ultimately to depression in the long run (21). PCOS may also be associated with several factors, such as insulin resistance and obesity, which may further aggravate the endocrine disorder during adolescence and increase the dysregulation of the HPA axis. Likewise, PCOS also leads to higher levels of androgen in the body, which is closely related to the risk factors of mental diseases (22), so there is speculation that pathological factors such as insulin resistance, obesity and high levels of androgen play a role in the occurrence of depression in PCOS (23). Hormonal drugs, like Ethinylestradiol cyproterone acetate tablets, are often used to treat PCOS. These drugs affect the cortical and subcortical areas of the brain that control emotions. These areas are immature and oversensitive in adolescents, which greatly increases the risk of depression (24). A lack of control over menstrual irregularities (11), as well as a lack of knowledge and information about the disease, which increases the psychological burden of the patients and may worsen depression (25). It can be seen that depression in PCOS is linked to the above-mentioned factors directly or indirectly. It's difficult to predict depression risk from one or more of these factors with any certainty because the number and magnitude of influencing factors are still inconclusive (Figure 1). Thus, developing a warning depression model for adolescents with PCOS through the interaction of complex influencing factors is a critical problem that requires immediate research, and there is no such report currently available.

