#### Exclusion criteria

Participants with cognitive impairment and major mental illness (36)(schizophrenia, schizoaffective disorder, bipolar disorder, etc.) (37).Participants with serious comorbidity(Other diseases that seriously affect the patient's normal life, such as acute myocardial infarction, systemic lupus erythematosus complicated by severe renal dysfunction, etc.).Other conditions that lead to elevated androgen levels (congenital adrenal cortical hyperplasia, Cushing syndrome, androgen-secreting tumors, etc.) and cause ovulation disorders (hyperprolactinemia, premature ovarian failure, functional hypothalamic amenorrhea, thyroid dysfunction, etc.).

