**Diagnosis and treatment factors**			
Medication use	Adolescents with PCOS taking some medications, such as metformin, oral contraceptives and so on. If yes, please specify the medicine	Binary & Categorical	0 “No” 1 “Yes” (medications classified into approximately four to five categories)
Duration of medicine use	Duration of medicine use since first diagnosis of PCOS	Categorical	Duration of medicine use classified into approximately five to six categories

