The study is a retrospective cohort study, and the questionnaire will be partially completed by patients' recollection of recent events, which may be subject to a degree of recall bias. In prospective cohort studies, depression outcomes and factors contributing to depression can be longitudinally tracked over a period of time of high-risk groups with PCOS in adolescence, which can help to make models more robust and representative. Data for this study will be collected at one hospital, so it will be a single-center study. It is proposed that future studies should collect data from multiple hospitals simultaneously to increase sample size and persuasiveness. In this study, participants will be selected in accordance with the diagnostic criteria prescribed in the “Chinese guidelines for diagnosis and treatment of polycystic ovary syndrome.” Due to the inconsistency in diagnostic criteria among different ethnic groups, the generalizability of this study is limited to some degree. It is recommended that metformin and oral contraceptives be used to treat PCOS in adolescence, in accordance with international evidence-based guidelines (4). It has been reported, that oral contraceptives may increase participants' risk of depression (24), whereas metformin can help to alleviate depression (52). Hence, confounding effects may occur if participants take metformin and oral contraceptives concurrently. As part of our investigation, we will assess the medication status of the participants. However, we will not be able to eliminate the possibility that there may be a confounding effect. The model was externally validated using temporal validation, as the data source is the same as the model development cohort, which may be less transferable and generalizable than geographical validation (which validates the model against data from other centers or even other countries).

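### Controls called normal girls are recruited at the gynecology clinic, and medication is defined only for girls with PCOS, so any PCOS-versus-control comparison is open to bias of unknown direction

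*Protocol article*

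**What the plan says.** The abstract (Methods and analysis) describes two groups: "The study will involve normal adolescent girls as the control group and adolescent PCOS patients as the experimental group". The Patient recruitment section gives the source: "Additionally, a control group will be recruited from the gynecology clinic among healthy, age-matched adolescent girls". Sample size and calculation sets 400 controls beside an estimated 800 girls with PCOS.

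Table 1, under Diagnosis and treatment factors, defines medication use as "Adolescents with PCOS taking some medications, such as metformin, oral contraceptives and so on" and its duration as "Duration of medicine use since first diagnosis of PCOS".

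The article treats these drugs as relevant to the outcome. The Introduction says that hormonal drugs used for PCOS act on emotion-controlling brain areas in adolescents and raise the risk of depression. The Discussion says that oral contraceptives may raise that risk and that metformin may relieve depression. The confounding it then concedes is of one kind: "Hence, confounding effects may occur if participants take metformin and oral contraceptives concurrently".

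The Objectives concern a model for adolescents with PCOS only. However, Statistical analysis methods lists two-group tests, and the end of the Introduction and the Discussion both extend the model's use to adolescent girls in general.

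**The concern.** There are two separate weaknesses, and both bear on the control group.

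The first is the source. A hospital gynecology clinic is not an obvious place to find girls who represent the normal population. The word healthy is the only safeguard, and the reason for attendance is not among the listed variables. The Exclusion criteria remove conditions that raise androgens or "cause ovulation disorders (hyperprolactinemia, premature ovarian failure, functional hypothalamic amenorrhea, thyroid dysfunction, etc", but the article does not say whether they apply to controls. Even if they do, other gynecological complaints remain possible.

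The second is measurement. A control can take an oral contraceptive, but as worded neither medication item has a meaning for her. A variable that the article itself regards as a determinant of depression is therefore undefined in one of the two groups.

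At stake is whether a difference between the groups, or the lack of one, can be read as PCOS against normal girls, and whether the controls can support use of the model beyond PCOS.

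**Working it through.** **The plan's own figure.** The stated minimum of 369 reproduces: (1.96/0.05)² × 0.4 × 0.6 = 368.79, rounded up to 369. It concerns the precision of a single proportion and does not involve the controls. The article gives no hypothesis, estimand or power for a between-group comparison, so there is no planned contrast to recompute. What follows is illustration only.

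**Starting point.** The Introduction states: "Adolescent girls with PCOS are 2.4 times more likely to suffer from depression than normal girls of the same age, about 50–60" (a percentage). Reading 2.4 as a risk ratio, depression in normal girls would be 0.50/2.4 = 20.8% to 0.60/2.4 = 25.0%.

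**Selection of controls (multipliers assumed).** Suppose depression in clinic-recruited controls is k times that in normal girls. The observed ratio is then 2.4/k.

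| k (assumed) | Control depression | Observed ratio | Power, 400 v 800, two-sided 5% |
|---|---|---|---|
| 1.25 | 26.0–31.2% | 1.92 | above 0.99 |
| 1.5 | 31.2–37.5% | 1.60 | above 0.99 |
| 2 | 41.7–50.0% | 1.20 | 0.78–0.91 |

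If k = 1, which is what healthy would mean if applied strictly, nothing changes. The article gives no value for k. At these sample sizes the difficulty is mainly one of interpretation, since power is lost only at the extreme.

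**Medication (risk ratios and use assumed).** Suppose a drug multiplies depression risk by R and is used by a share a of PCOS girls and b of controls. The crude ratio is then multiplied by [a(R − 1) + 1]/[b(R − 1) + 1].

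- R = 1.2, a = 30%, b = 0: 1.06/1.00 = 1.06
- R = 2.0, a = 70%, b = 0: 1.70/1.00 = 1.70
- R = 1.2, a = 50%, b = 30%: 1.10/1.06 = 1.04
- R = 2.0, a = 50%, b = 30%: 1.50/1.30 = 1.15

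The factor falls below 1 if the drug lowers risk (R < 1) and PCOS girls use it more, which is what the Discussion suggests for metformin. It also falls below 1 if R > 1 and controls use the drug more than patients do.

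**Together.** If the two biases combine by multiplication, the net factor on the ratio runs from 1.04/2 = 0.52 to 1.70/1.25 = 1.36. It spans 1, so even within these assumed ranges the sign of the net bias is undetermined.

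**What cannot be repaired in analysis.** To adjust for medication, b must be observed. With Table 1 followed as written, b is not defined.

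**The case against.** The strongest reply is that no PCOS-versus-normal contrast is an objective. Both aims, and all three questions in the Discussion, concern adolescents with PCOS, and the model-building and validation sections give controls no role. This stands: the PCOS model does not depend on who the controls are. It does not dispose of the point, because the abstract makes the controls part of the design, they are 400 of 1,200 planned girls (one third), two-group tests are listed, and they are the only non-PCOS data that could support the extension to general girls.

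A second reply is that Table 1 lists model predictors and is not the controls' data form, and that the Discussion promises to assess participants' medication. This has some force. Use in controls is undefined in the article; it is not shown to be unrecorded in practice or to be uneven. But Table 1 is the only definition given, and the medication confounding conceded does not extend to differences between groups.

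A third reply is that same-clinic controls share catchment and referral and are a recognised choice, and that detailed control criteria commonly sit in the full protocol. Both parts are fair. The absence of a definition of healthy is not, on its own, the finding.

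A reader might go further and infer that symptomatic clinic controls dilute the contrast towards no difference. The article does not support this. It gives neither the controls' reasons for attendance nor their depression rate, and heavier hormonal-drug use in PCOS girls would push the contrast the other way. Any calculation that assumes a control rate above the normal rate builds the dilution in.

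**Conclusion.** The point holds for between-group comparisons and for the claim about general girls, not for the prediction model within PCOS. The label (normal) and the source (gynecology clinic attenders) do not match without evidence on why controls attend. The medication items are worded so that they cannot be applied to controls, despite the article's own statements that these drugs affect depression. A PCOS-versus-control comparison is therefore open to selection bias and to medication confounding that cannot be adjusted for.

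The size cannot be derived from the article. The ratios of 1.92 to 1.20, the drug factors of 1.04 to 1.70 and the net range of 0.52 to 1.36 rest on assumed control depression rates, drug effects and shares of use, and on reading 2.4 as a risk ratio. They show only that either bias could matter and that the net direction is unknown. They are not evidence that this study's contrast is too small or too large.

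**What to change.** 1. In Table 1, reword the two medication items to the participant's current medications and the duration of their use, without reference to PCOS diagnosis. Complete them in both groups and adjust any between-group comparison for them.
2. Record each control's reason for attending the clinic and any gynecological diagnosis. Report the comparison with and without symptomatic attenders.
3. Unless controls are shown to attend for non-disease reasons, call them gynecology outpatients without PCOS in place of normal or healthy girls, and limit the statements in the Introduction and Discussion about general adolescent girls accordingly.

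Controls who use hormonal drugs should not be excluded as part of this fix. That would leave no hormone-exposed controls and make PCOS harder to separate from its treatment.

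The cost is one reworded form item, the attendance and diagnosis record for controls, and a less general label for the comparison. The PCOS model and its sample size are untouched. Medication and reason for attendance should be captured at the visit, since they are hard to recover afterwards.

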### Eligibility criteria

#### Inclusion criteria

Aged 10–19 years old (33).According to “Chinese guidelines for diagnosis and treatment of polycystic ovary syndrome,” which was developed by the Endocrinology Group of the Chinese Medical Association Obstetrics and Gynecology Branch in 2018 (34), PCOS participants in the study must meet all three indicators in the Rotterdam diagnostic criteria at the same time (35), including: (i) oligomenorrhea persisting for at least 2 years after menarche, or amenorrhea; (ii) clinical manifestations of hyperandrogenism or hyperandrogenemia; (iii) the diagnosis of PCO on ultra sound includes increased ovarian size (>10 cm^3^).Able to self-report (verbally understandable and articulate).Participants and their families volunteer to participate in the study.

#### Exclusion criteria

Participants with cognitive impairment and major mental illness (36)(schizophrenia, schizoaffective disorder, bipolar disorder, etc.) (37).Participants with serious comorbidity(Other diseases that seriously affect the patient's normal life, such as acute myocardial infarction, systemic lupus erythematosus complicated by severe renal dysfunction, etc.).Other conditions that lead to elevated androgen levels (congenital adrenal cortical hyperplasia, Cushing syndrome, androgen-secreting tumors, etc.) and cause ovulation disorders (hyperprolactinemia, premature ovarian failure, functional hypothalamic amenorrhea, thyroid dysfunction, etc.).

### Determinations and variables

After discussion and conclusion, the research team obtained indicators of independent and dependent variables affecting depression in PCOS adolescents, as follows.

#### Dependent variables

Depression will be measured by the Chinese version of the Children's Depression Scale(CDI) (38). The scale is comprised of 27 items, each of which offers three possible replies based on the respondent's actual mood during the previous 2 weeks. The project consists of five dimensions: anhedonia, poor efficacy, low self-esteem, negative emotions, and interpersonal problems. The intensity of each item determined whether it was rated zero, one, or two, and the negative word statement was scored in reverse. A score of 19 indicated the presence of depressive symptoms. It has been reported that the Chinese version of the CDI scale has been applied to children and adolescents ranging from 7 to 18 years of age in China (38–40). CDI has the advantage of having the lowest reading level of all depression measurement tools (only the first grade level). The Chinese version of the CDI scale has a good level of reliability and validity, as well as a high clinical diagnostic value for depression, and can be used to measure depression in children and adolescents in China. Utilize the total score to reflect the severity of depressive symptoms or diagnostic threshold due to its operability and clinical applicability.

We will use the Kiddie-Schedule for Affective Disorders and Schizophrenia-Epidemiological version (K-SADS-E) to confirm the diagnosis of depression and exclude possible comorbidities. The validated Mandarin version will be used in this study (41). It is a semi-structured diagnostic interview questionnaire designed to assess the current and past mental health status of children and adolescents aged 6-18 in accordance with the diagnostic criteria of the Diagnostic and Statistical Manual of Mental Disorders, 5th edition (DSM-5). In this study, two psychiatrists trained in K-SADS-E interview harmonization will conduct interviews to diagnose depression and exclude possible comorbidities. It will take approximately 1–1.5 h for each participant and their parents to complete the interview. It has been demonstrated that K-SADS-E has good psychometric properties (41). The diagnoses of K-SADS-E demonstrated good convergent and divergent validity with most corresponding clinical questionnaires.

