## Abstract

**Introduction:**

The high prevalence and severity of depression in adolescents with polycystic ovary syndrome (PCOS) is a critical health threat that must be taken seriously. The identification of high-risk groups for depression in adolescents with PCOS is essential to preventing its development and improving its prognosis. At present, the routine screening of depression in adolescents with PCOS is mainly performed using scales, and there is no early identification method for high-risk groups of PCOS depression in adolescents. It is necessary to use a warning model to identify high-risk groups for depression with PCOS in adolescents.

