
Depression high-risk groups are individuals or subgroups who suffer from certain depressive symptoms but do not meet the diagnostic criteria for depression (17). They constitute a mental sub-health state between health and depression. Given the high prevalence of depression in adolescents with PCOS, warning of its onset risk and identification of high-risk groups is significant for preventing its development and improving its prognosis (18). There is currently no early detection approach for high-risk groups of depression in adolescents with PCOS, and most routine screening uses questionnaires. Hence, it's necessary to develop a warning model to identify adolescents with PCOS at high risk for depression.

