
## Objectives

The aims of the study are to: (i) Develop a depression prediction model for adolescents with PCOS to identify at-risk populations early; (ii) Validate the accuracy and validity of the model and to assess the clinical utility of the model.

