**Individual susceptibility factors**			
Age	Adolescent's age	Continuous & Categorical	Years (age classified into approximately three to four categories)
Nationality	Adolescent's nationality	Binary	0 “the Han nationality” 1 “minority nationality”
Body mass index(BMI)	Body mass divided by the square of the body height	Continuous	kg/m^2^
Waist-to-hip ratio (WHR)	WHR is found by dividing circumference of the waist by the circumference of the hips	Continuous	
Living residence	Current residence of adolescents	Binary	0 “City” 1 “Countryside”
Education level	Current educational level of adolescents	Categorical	Education level classified into approximately five categories
Single parent family	Adolescents live with only one parent	Binary	0 “No” 1 “Yes”
Family history of mental illness	Mental illness within three generations in the paternal, maternal, direct and collateral lines in adolescents	Binary	0 “No” 1 “Yes”
Duration of illness	Time since first diagnosis of PCOS	Categorical	Duration of illness classified into approximately five to six categories
Personality	Eysenck Personality Questionnaire-Junior (42)	Continuous	
Emotional regulation skills	Emotion Regulation Scale (43)	Continuous	

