**Psychosocial environmental factors**			
Interpersonal sensitivity	Symptom Checklist-90 (45)	Continuous	
Social support	Medical Outcomes Study Social Support Survey (46)	Continuous	

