**Clinical symptoms**			
Hirsutism	Ferriman-Gallwey Rating Scale (47)	Continuous	
Acne	Rosenfield Scale (48)	Continuous	
Body image	The Nagetive Physical Self Scale (49)	Continuous	

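### Self-report scales that partly overlap the CDI are taken in the same session as the outcome and enter a single LASSO, so a high C-statistic could not be told apart from concurrent measurement of depressive symptoms

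*Protocol article*

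**What the plan says.** **Rationale and aim.** The Abstract (Introduction) states that "the routine screening of depression in adolescents with PCOS is mainly performed using scales, and there is no early identification method" for high-risk groups. The Introduction repeats that "most routine screening uses questionnaires". The first aim under Objectives is to "Develop a depression prediction model for adolescents with PCOS to identify at-risk populations early"; the second includes assessing clinical utility.

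**Outcome.** Under Dependent variables, depression is measured with the CDI: 27 items on the previous two weeks, with a threshold of 19. Its five dimensions are "anhedonia, poor efficacy, low self-esteem, negative emotions, and interpersonal problems". A K-SADS-E interview by psychiatrists is to confirm the diagnosis. The text does not say which of the two is the outcome in the model.

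**Candidate predictors.** Table 1 lists seven questionnaire-based predictors: personality, emotional regulation, insomnia, interpersonal sensitivity, social support, body image (negative physical self) and illness perception. One row reads "Interpersonal sensitivity Symptom Checklist-90 (45) Continuous". The table also lists demographic and clinical variables, treatment, and eleven laboratory measures.

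**Timing.** Under Data collection, the interview, the online scales and the recording of laboratory values form one process of about two hours.

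**Analysis.** Model-building procedures and Internal validation describe one LASSO over all predictors, with lambda chosen by the one-standard-error rule. Variables with zero coefficients are dropped, and those that remain are read as the factors associated with depression. Performance is judged by the C-statistic and a calibration plot. No reduced model and no comparison with the CDI is stated.

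**The concern.** The model is offered as an advance on screening by questionnaire, yet much of its predictive information may come from questionnaires completed alongside the outcome. Where a predictor scale covers the same ground as a CDI dimension, its association with the outcome reflects, at least in part, the same current state measured twice.

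Two things are at stake. First, the headline C-statistic would not show how much discrimination comes from information that routine PCOS care already holds, nor whether the model does better than giving the CDI itself. Both bear directly on the stated objectives. Second, the one-standard-error rule favours a small model. If overlapping scales absorb the signal, weaker terms for androgens, BMI or treatment may be shrunk to zero and read as unimportant, although the Discussion promises to say which factors influence depression and what role each type plays.

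**Working it through.** **Step 1: set the predictors against the CDI dimensions.** Item content is not given, so this comparison is by name only.

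| CDI dimension | Candidate predictor | Match |
|---|---|---|
| Interpersonal problems | SCL-90 interpersonal sensitivity | Clear by name |
| Negative emotions | Emotion regulation | Plausible |
| Low self-esteem | Negative physical self | Plausible |
| Anhedonia | None named | None |
| Poor efficacy | None named | None |

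The overlap therefore covers one to three of the five dimensions.

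**Step 2: the plan's own figure.** Sample size and calculation assumes an outcome proportion of 0.4 and a margin of error of 0.05:

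n = (1.96/0.05)² × 0.4 × 0.6 = 1536.64 × 0.24 = 368.79, rounded up to 369, as stated.

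This figure does not bear on the point, but it supplies the prevalence of 0.4 used below.

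**Step 3: what one overlapping scale could produce.** The article gives no correlations, so these are assumed. The model is a standard normal CDI score, with the top 40% counted as depressed, and a predictor with correlation r to that score. The C-statistic is the probability that a random case scores above a random non-case, estimated from 400,000 simulated draws.

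| r | 0.2 | 0.3 | 0.4 | 0.5 | 0.6 | 0.7 |
|---|---|---|---|---|---|---|
| C at prevalence 0.4 | 0.592 | 0.638 | 0.685 | 0.732 | 0.781 | 0.832 |

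Prevalence matters little. At r = 0.6, C is 0.797 at prevalence 0.2 and 0.781 at prevalence 0.6.

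**Step 4: three overlapping scales together.** If each has correlation r with the CDI and c with each of the others, the multiple correlation satisfies R² = 3r²/(1 + 2c). For r = 0.5 and c = 0.5, R² = 0.75/2 = 0.375, so R = 0.612.

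| r of each scale | R at c = 0.5 | C | R at c = 0.3 | C |
|---|---|---|---|---|
| 0.3 | 0.367 | 0.669 | 0.411 | 0.691 |
| 0.4 | 0.490 | 0.726 | 0.548 | 0.755 |
| 0.5 | 0.612 | 0.786 | 0.685 | 0.823 |
| 0.6 | 0.735 | 0.850 | 0.822 | 0.897 |

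With moderate correlations (0.5 to 0.6), the three scales alone would give C of about 0.79 to 0.90, with nothing from any PCOS variable. With weak correlations (0.3) they would give only 0.67 to 0.69. The planned single model cannot show which case applies.

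**The case against.** - **The target is symptom-based.** The Introduction defines high-risk groups as people with some depressive symptoms who fall short of a diagnosis. Predictors close to symptoms suit that target, and the article never promises a model free of scales. This stands: including the scales is legitimate. It does not supply the missing comparison.
- **The scales are candidates.** A reader might infer that the model needs all seven instruments. It does not: LASSO may drop some, and the final number is unknown.
- **The overlap is partial.** A reader might infer that the predictors duplicate the CDI. Names alone support one clear match and two plausible ones.
- **The K-SADS-E may be the outcome.** If so, shared self-report method is reduced. Measurement in the same session remains.
- **Displacement is not certain.** LASSO selects on joint contribution, so PCOS variables with independent signal can survive. Nor are all the scales rivals to the claimed novelty: the Discussion counts illness perception as part of it, and body image is filed under clinical symptoms.
- **Extra models may be left to an analysis plan.** An article need not list every secondary analysis. But this one fixes the predictor list, the timing and a single-model procedure, and as fixed these cannot answer its own objectives. Its limitations mention recall bias and the advantage of prospective follow-up, but not overlap between predictors and outcome.

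**Conclusion.** The concern holds in a limited form. As described, a high C-statistic could not be told apart from concurrent measurement of depressive symptoms. The plan could show neither what routine PCOS information adds nor whether the model improves on the 27-item CDI.

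A reader might go further and conclude that a high C-statistic would simply be depression measured again. The document does not support that: discrimination could come partly from overlap and partly from genuine risk factors. Nor would removing the scales yield an early-identification model, because the remaining predictors are set against the same current outcome in the same session.

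The size is conditional. About 0.64 (r = 0.3) to 0.83 (r = 0.7) for one scale rests on assumed correlations, a normal CDI score and 40% prevalence. This is a worthwhile and inexpensive improvement, and it does not make the study invalid.

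**What to change.** Prespecify two nested models on the same data:

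- **(a) Routine-care predictors only:** demographics, BMI and waist-to-hip ratio, family history, illness duration, medication, hirsutism, acne and laboratory values.
- **(b) Model (a) plus the self-report scales.**

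Report the C-statistic and calibration for both, and the gain from (a) to (b). With the K-SADS-E diagnosis as reference, report the C-statistic of the CDI total alone as a benchmark, and assess (a) and (b) against that same reference so that the figures are comparable. This relies on all participants being interviewed, as Data collection describes.

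Describe both models as detection of current depression, and base no early-identification claim on either. Do not read a zero coefficient for a PCOS variable in (b) as evidence that it is unimportant without looking at (a).

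The cost is one extra model fit and one benchmark on data already planned. The routine-care model will probably have a less favourable C-statistic than the full model.
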